### Objectives:

Primary objective:

- (iv) To develop Balika Bodhu, a social norm intervention combining empowerment of MAGs and mobilisation of relevant stakeholders to promote demand for, access to, and practices of SRHR, including FP use, conception and SRH service uptake.

- (v) To measure the effect of Balika Bodhu in increasing demand for, access to, and practices of SRHR (FP use, conception, and SRH service uptake) of MAGS.

**Secondary objectives:**

- (vi) To measure the effect of Balika Bodhu on empowerment of MAGs;  
(vii) To measure the effect of Balika Bodhu on social norm regarding SRHR of MAGs;  
(viii) To explore how change happens or why change does not occur.

**Methods:**

Balika Bodhu will involve a mixed-method two-arm (intervention and control) Cluster Randomized Controlled Trial (CRCT) design. Balika Bodhu will be implemented in 32 clusters (villages, primary sampling unit) in Rajbari Sadar *upazila* of Rajbari district. The clusters will be formed and randomized to two study arms. The study will employ both quantitative and qualitative methods to test the impact of Balika Bodhu to promote demand for, access to and practices of SRHR, including FP use, conception and SRH service uptake. A total of 1120 MAGs will be randomly selected (35 per cluster) from the list obtained through household enumeration. Their husbands will also be included in the study. Both the MAGs and their husbands will be surveyed at baseline, will be provided with the intervention in the intervention clusters and will be surveyed at endline. Randomly selected cross sectional samples of community members aged 35-59 years will also be surveyed at baseline and endline. Qualitative data will be collected at baseline and endline from two intervention clusters using 32 In-depth Interviews (with 16 MAGs and 16 husbands of MAGs), and 6 Key Informant Interviews (with mothers-in-law of MAGs, NGO staff, CHWs, village doctors/ traditional healers/ drug sellers) and 8 Focus Group Discussions (with MAGs, their spouses, and elderly women/influential community members aged 35-59 years).

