### **Household enumeration, sampling and recruitment of study participants**

Once the clusters have been selected and randomized to intervention and control arms, an enumeration of the households in each cluster will be conducted to collect socio-demographic information on the household members (e.g., sex, date of birth, age and marital status) to form the sampling frame for the MAGs', their husbands' and the community survey. We will also collect information on whether the MAGs living with husband or not for determining whether or not they are eligible for participating in the intervention. A properly trained team of data collectors will conduct this enumeration. Special care will be taken to train them on how to collect and check information on age. The MAGs aged between 15 and 19 years, currently living with husband and living in the study village will be considered as eligible to participate in this study. Adult male and female community members who are aged 35-59 years and currently living in the study village will be considered as eligible.

From the list of eligible MAGs in a cluster, we will randomly select 35 MAGs using a computer-generated sequence, once again by the same independent statistician. The number 35 was calculated assuming a 10% non-response in the baseline survey and another 20% of the MAGs/husbands of MAGs may refuse to participate in the intervention, which will make the MAG and husband of MAG groups size 25 for the group sessions in each cluster. If any cluster consists of less than 35 MAGs, one portion of the most adjacent village will be included as a part of the cluster to make the number of MAGs 35. The community survey sample will also be selected randomly using a computer-generated sequence by the same statistician.

Upon receiving consent, the selected MAGs and their husbands will be enrolled in the study and included in the baseline survey. Following the baseline survey interviews, MAGs from the intervention villages will be invited to participate in the Balika Bodhu intervention, and upon receiving their consent, they will be formally enrolled in the intervention. All MAGs and their husbands who were interviewed at baseline will also be targeted for follow-up interviews at the endline.

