#### ***Inclusion and exclusion criteria for clusters***

Any village with around 500 households or 35 MAGs will be considered as eligible to be included in this study.

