### **Intimate partner violence (IPV)**

MAGs' experience of IPV (i.e. controlling behaviour, and physical and sexual violence IPV) will be measured using a modified version of The Revised Conflict Tactic Scale (Straus et al., 1996). The scale is the most widely used measure of IPV which is characterized by having direct and behaviorally explicit questions in order to reduce variation in the interpretation and understanding of what violence comprises of. These instruments are designed to minimize reporting biases that arise from subjective perceptions of abuse by asking only about specific behaviours perpetrated by a male partner (e.g., "Has your husband or any other family member ever slapped you or threw something at you that could hurt you?"). Questions will capture behaviours that reflect minor and severe physical violence (e.g., slapped, pushed, hit with a fist, kicked, dragged, choked, burned, threatened with a weapon); and sexual violence (e.g., forced sexual intercourse or other sexual acts). To measure economic coercion, we will use a modified version of the ECS-20 (Yount et al., 2022). Typical items include—your husband or any other family member ever and in last 12 months: disallowed you to go to your work, school or training, or do any home-based income earning activity; told that you could work outside the home only if you kept up with the housework; told that you could earn income only if you worked from home; etc. A woman will be considered exposed to any specific type of IPV if she responds "yes" to any of the items related to that specific type of IPV, and will be coded "yes=1", and "no=0" otherwise.

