## **Ethical considerations**

The study will seek ethical approval from icddr,b's institutional review board. Informed consent will be obtained from the study participants. Participation in the study will be as entirely voluntary. Individual verbal consent will be sought by the interviewer prior to the interview with each study participant. The MAGs who are minor (aged below 18) will be considered as "mature minors" and following the guidelines for adolescent health research published by the National Commission for the Protection of Human Subjects of Biomedical and Behavioral Research and the Society for Adolescent Medicine (Society for Adolescent Medicine, 2003; National Commission for the Protection of Human Subjects of Biomedical and Behavioral Research, 1977) we will seek informed consent from them.

According to English et al., (1995), mature minors are those who are living apart from their parents, married, pregnant, parents themselves, and self-supporting and they are allowed to give consent (English et al., 1995). In our study, we will consider MAGs aged below 18 as "mature minors" as all of them are married and some of them are expected to be pregnant and/or have child/ren. Thus, the mature minors in this study do not require consent from a guardian.

The primary ethical purpose of obtaining consent of a guardian is to ensure that vulnerable children are protected from potential risks a research may pose. However, this approach does not always protect a minor (National Commission for the Protection of Human Subjects of Biomedical and Behavioral Research, 1977), and may be problematic in some situations as well (Department of Health and Human Services, National Institutes of Health, Office for Protection from Research Risks, 2001). Examples of such situations, where parental permission is not appropriate and is not a reasonable requirement include, abuse, contraception use, etc.). Most of the MAGs will be living not with their parents, but with their husbands and in-laws, usually considered as their guardians. Since our study deals with sensitive issues such as sexual and reproductive coercion and violence, where the most common perpetrators are the husbands it would be unethical to leave it up to them to decide whether or not the girl will participate in the study. Informing the potential perpetrator about the study may also increase the risks of abuse of the girls. Due to these ethical concerns consent must not be obtained from the husbands.

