### ***Security and safety of study participants***

If the sensitive issues explored in the research becomes widely known - either within the household or among the wider community – both the MAGs giving interviews and the study team may be at risk of harm. Thus, the research will be introduced at the local and household levels as a study of young women's reproductive health and life experiences.

To assure safety of the married MAGs the spouses of the MAGs will not be asked about DV. Care will be taken to phrase the questions in the qualitative guides for the spouses in a manner to avoid sensitivities. All interviews will only be conducted in private in a location of the participant's choice. If confidentiality cannot be maintained for any reason the interview will be rescheduled (or relocate) at a time (or place) that may be more safe or convenient for the respondent.

Interviewers will be trained to terminate or quickly change the subject of discussion if an interview is interrupted by anyone. During the interview, the interviewer will forewarn the respondent that she will terminate or change the topic of conversation if the interview is interrupted, and will be able to skip to these questions at any point if needed. To ensure that interviewers gain experience about how to handle interrupted interviews, their training will include a number of roles play exercises simulating different situations that they may encounter.

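### The girls' draw has no one-per-household limit, so two girls in one household can both be given the violence questions, a route the safety measures do not cover

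*Protocol*

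**What the plan says.** The operative text is in the section on household enumeration, sampling and recruitment: "From the list of eligible MAGs in a cluster, we will randomly select 35 MAGs using a computer-generated sequence". The Project Summary says the same: "A total of 1120 MAGs will be randomly selected (35 per cluster) from the list obtained through household enumeration".

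Eligibility is set per girl: "The MAGs aged between 15 and 19 years, currently living with husband and living in the study village will be considered as eligible". The individual inclusion and exclusion criteria add migration plans and fitness to take part, but nothing about households.

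The draw can come close to taking every eligible girl. The cluster criteria state: "Any village with around 500 households or 35 MAGs will be considered as eligible to be included in this study". For smaller villages: "If any cluster consists of less than 35 MAGs, one portion of the most adjacent village will be included as a part of the cluster".

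On living arrangements, Ethical considerations says: "Most of the MAGs will be living not with their parents, but with their husbands and in-laws, usually considered as their guardians".

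The section on intimate partner violence gives a sample item that begins: "Has your husband or any other family member ever slapped you". The section on security and safety of participants warns of harm to girls and study team if the sensitive issues become widely known, "either within the household or among the wider community". It responds with a neutral description of the study, private interviews, rescheduling or relocation if confidentiality cannot be kept, a change of subject on interruption, and no questions to husbands about domestic violence.

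**The concern.** The violence items cover the husband and other family members. For two girls in one joint household, those relatives may be the same people, or one girl's husband may be the other girl's reported perpetrator. Once the first has been interviewed, someone in that household knows the full content of the violence module before the second is interviewed.

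The listed measures protect against an interview being overheard or the topic being announced. None deals with a second household member receiving the same questions. The protocol deliberately withholds domestic violence questions from husbands for the girls' safety; the draw leaves another way for that content to reach the household.

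At stake is the safety of girls aged 15 to 19 in a study that its own application form rates as greater than minimal risk.

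**Working it through.** **The plan's own figures.** Detecting 50% against 65% (the 15% effect read as absolute), two-sided 5%, 80% power, pooled-variance formula without continuity correction, needs 170 girls per arm. The design effect is 1 + (22 − 1) × 0.05 = 2.05. Then 170 × 2.05 = 348.5, and 348.5 / 22 = 15.84, so 16 clusters per arm as stated. Inflating for losses gives 22 / (0.9 × 0.8 × 0.85) = 35.9 against the stated 35, and 35 × 32 = 1,120. The sample size is not at fault and this point does not change it.

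**Inputs for the check.**
- From the protocol: 32 villages and 35 girls drawn per village.
- Assumed: *f*, the share of eligible girls who live with one other eligible girl. The documents give no value.
- Assumed: *M*, the number of eligible girls listed per village. The value 35 is the cluster criterion and means that every listed girl is drawn; 100 is taken as a generous upper value.

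**Formula.** A village has *M f* / 2 two-girl households. Both girls of such a household are drawn with probability 35 × 34 / [*M*(*M* − 1)]. The expected number of drawn two-girl households over all villages is

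E = 32 × (*M f* / 2) × 35 × 34 / [*M*(*M* − 1)],

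and the chance of at least one is about 1 − exp(−E).

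Lowest case in the main range, *f* = 0.5% and *M* = 100: 32 × 0.25 × 1,190 / 9,900 = 0.96. Highest case, *f* = 5% and *M* = 35: 32 × 0.875 × 1 = 28.

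| *f* | *M* = 35 | *M* = 50 | *M* = 70 | *M* = 100 |
|---|---|---|---|---|
| 0.1% | 0.56 | 0.39 | 0.28 | 0.19 |
| 0.5% | 2.8 | 1.94 | 1.38 | 0.96 |
| 1% | 5.6 | 3.89 | 2.76 | 1.92 |
| 2% | 11.2 | 7.77 | 5.52 | 3.85 |
| 5% | 28.0 | 19.43 | 13.8 | 9.62 |

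The chance of at least one such household, from *M* = 35 to *M* = 100, is 94% to 62% at *f* = 0.5% and 99.6% to 85% at *f* = 1%. At *f* = 0.1% it is 43% to 17.5%, so only near that value does the event become unlikely.

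**Allowing for non-response.** With the protocol's 10% baseline non-response, taken as independent between the two girls, both are interviewed in 0.9 × 0.9 = 81% of drawn pairs. The main range of 0.96 to 28 becomes about 0.8 to 23 households.

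**After the change.** With one girl per household in the frame, the count is zero by construction. The frame loses *M f* / 2 girls per village. At *M* = 35 that is 0.09 (*f* = 0.5%) to 0.88 (*f* = 5%).

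**The case against.** Several counter-arguments carry weight.

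- **No rule is broken.** A reader might infer that the plan contradicts its own ban on the topic becoming known in the household. The safety section contains no ban. It names a conditional risk and a mitigation. This is an omission that sits badly with a stated concern, not a contradiction.
- **The event is not certain, and its size is unknown.** A reader might scatter 35 girls at random over 500 households and obtain C(35,2)/500 = 1.19 pairs per village, or about 38 pairs in 32 villages. Nothing in the documents supports random placement, and about 500 households is the lower limit for a village. Likewise, 2% co-residence implies 11.2 households (about 22 girls) only if nearly every listed girl is drawn; with 100 listed it is 3.85 (about 8 girls).
- **Other routes to household knowledge remain.** Husbands are surveyed on attitudes to violence against women, and in the intervention arm they attend sessions that cover gender-based violence. Community members answer similar attitude items. This stands, so the limit gives only partial protection. Those items ask about attitudes, however, while a second girl is asked about experienced violence.
- **Guarded answers are not shown.** A reader might infer that the second girl would disclose less and so bias the violence outcome. The documents offer no support for this, the draw is the same in both arms, and intimate partner violence is a secondary outcome. The case should rest on safety.
- **The change is not free.** It shrinks the frame and makes selection probabilities unequal.

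The existing safeguards are real, but they address overhearing and announcement, not two interviews in one household.

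**Conclusion.** The point holds as a safety gap in the sampling rule. As written, the draw permits two girls in one household to receive the full violence module, and the stated protections do not reach that case. Under the assumed range (0.5% to 5% co-residence, 35 to 100 girls listed per village) about 1 to 28 such households would be drawn across 32 villages. At 1% or more, at least one is likely throughout the range (85% or higher). These figures rest on co-residence rates and list sizes that the documents do not give, and on shared households holding exactly two eligible girls.

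The documents do not support saying that a protocol rule is violated, that a particular number of girls will be affected, or that outcome data would be biased. The sample size calculation is unaffected.

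**What to change.** In the section on household enumeration, sampling and recruitment, add one step before the draw: where the enumeration shows more than one eligible girl in a household, the independent statistician first selects one at random, then draws the 35 from this one-per-household frame. Repeat the limit in the Project Summary. Where a village is topped up from its neighbour, apply the limit to the combined list.

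The girl not selected should not be invited to the sessions without being surveyed. Under the recruitment section, invitations follow the baseline interview, and such a girl would be a participant without outcome data.

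**Cost.**
- One sentence and one extra operation, as enumeration already precedes the draw and collects data on household members.
- A slightly smaller frame. A village near 35 girls may need the existing adjacent-village top-up, which draws on land near the planned buffer zones.
- A girl in a two-girl household has half the selection probability of other girls in the frame. This touches only the share *f* of girls.

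The target of 35 per village and 1,120 in total does not change.

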**Outcome measures/variables:**

***Primary outcomes:***

1. Instrumental agency of MAGs in decision making regarding SRHR (i.e., FP use; timing of first conception; and number of children to have)

***Secondary outcomes:***

Secondary outcomes that will be measured among the MAGs:

2. Intrinsic agency of MAGs
3. Instrumental agency of MAGs
4. Collective agency of MAGs
5. Critical consciousness (perceived inequality, egalitarianism and critical action) regarding gender inequality in the society
6. Knowledge of MAGs regarding FP and conception
7. Positive attitudes of MAGs regarding FP and conception
8. Couple communication initiated by MAGs regarding FP use, timing of first conception, and number of children to have
9. MAGs attempts to negotiate FP use, timing of first conception, and number of children to have as per her choice
10. Service uptake among MAGs regarding abortion and post-abortion care, and help seeking after experiencing violence
11. Prevalence of intimate partner violence (IPV) among the MAGs

Secondary outcomes that will be measured among the husbands of MAGs:

12. Knowledge of husbands of MAGs regarding FP and conception
13. Positive attitudes of husbands of MAGs regarding FP and conception
14. Positive attitudes regarding agency of MAGs regarding SRHR among the husbands
15. Non-condoning attitudes of husbands of MAGs regarding violence against women
16. Positive attitudes of husbands of MAGs regarding gender roles within household

Secondary outcomes that will be measured among the community members:

17. Knowledge of community members regarding FP and conception
18. Positive attitudes of community members regarding FP and conception
19. Positive attitudes regarding agency of MAGs regarding SRHR among the community members
20. Positive attitudes of community members regarding violence against women
21. Positive attitudes of community members regarding gender roles within household

Secondary outcomes that will be measured among both the MAGgs and the community members:

22. Positive social norms regarding SRHR of MAGs

## Description of the Research Project

### Hypothesis to be tested:

In a hypothesis testing research proposal, briefly mention the hypothesis to be tested and provide the scientific basis of the hypothesis, critically examining the observations leading to the formulation of the hypothesis.

Does this research proposal involve testing of hypothesis: ☐ No ☒ Yes (describe below)  
Hypotheses:

Balika Bodhu, a social norm intervention on sexual and reproductive health and rights (SRHR) combining a comprehensive empowerment package for married adolescent girls (MAGs) and positive engagement of relevant stakeholders will significantly improve demand, access and practices regarding SRHR among MAGs in FP use, conception and SRH service uptake (See Figure 1 and pages 21-22 for details).

### Specific Objectives:

Describe the specific objectives of the proposed study. State the specific parameters, gender aspects, biological functions, rates, and processes that will be assessed by specific methods.

Primary objective:

- (1) To develop Balika Bodhu, a social norm intervention combining empowerment of MAGs and mobilisation of relevant stakeholders to promote demand for, access to, and practices of SRHR, including family planning (FP) use, conception, and SRH service uptake.
- (2) To measure the effect of Balika Bodhu in increasing demand for, access to and practices of SRHR (FP use, conception, and SRH service uptake) of MAGS.

Secondary objectives:

- (3) To measure the effect of Balika Bodhu on empowerment of MAGs;
- (4) To measure the effect of Balika Bodhu on social norm regarding SRHR of MAGs;
- (5) To explore how change happens or why change does not occur.

### Background of the Project including Preliminary Observations:

Provide scientific validity of the hypothesis based on background information of the proposed study and discuss previous works on the research topic, including information on sex, gender and diversity (ethnicity, SES) by citing specific references. Critically analyze available knowledge and discuss the questions and gaps in the knowledge that need to be filled to achieve the proposed aims. If there is no sufficient information on the subject, indicate the need to develop new knowledge.

Sexual and reproductive health and rights (SRHR) are vital to one's health and development. It is recognised as essential for achieving social justice (Cepal, 2013). According to the Guttmacher–Lancet Commission, achieving SRH rests on realizing sexual and reproductive rights including the right to control one's own body, define one's sexuality, choose one's partner, and receive confidential, respectful, and high-quality health services (Starre, 2018). However, denial of SRH rights and limited access to the full set of SRHR services to females have been pervasive in many countries and particularly in countries with patriarchal social structures, where female power and status are compromised.

Over the last few decades Bangladesh, known as a patriarchal society, has made remarkable progress in improving contraceptive use, and maternal health (NIPORT & ICF, 2019; MoHFW, et al., 2015). However, the progress has not been consistent in different SRHR domains and is not uniform across different groups of reproductive aged females (UNFPA, 2016). Evidence suggests progress was particularly slow in realising SRH rights of the women (Naripokkho, 2017; BLAST, 2022) suggests that choice and consent of females are ignored in all spheres of SRHR and that patriarchal gender and social norms, and

discriminatory laws and practices in Bangladesh perpetuate denial of SRHR to females (Naripokkho, 2017; BLAST, 2022).

Marriage is almost universal in Bangladesh (Islam and Mahmud, 1996). Due to high prevalence of child marriage in Bangladesh (59%) (NIPORT & ICF, 2019) a huge proportion of adolescent girls are married before reaching 18. Since marriages are mostly arranged and village exogamy is largely practiced, most girls are cut off from their own networks as they join their marital family usually living in a different village. In a patriarchal setting such as Bangladesh with very strong gender and age hierarchies these child brides typically command the lowest power in the marital home. They typically have lower education than those who get married in adulthood. They also lack voice and bargaining skills (Gage, 2000; MacQuarrie, 2009; Shahabuddin et al., 2016). In such a context, the husband or mother-in-law may figure prominently in decisions about using contraception and the timing of childbearing (Barua and Kurz 2001; MacQuarrie and Edmeades, 2015) or she may begin childbearing as a way to improve her standing in the household (MacQuarrie 2009; MacQuarrie 2015). In this context, denial of SRHR usually becomes part of their lived experiences. For instance, they are commonly denied consent and choice regarding when to conceive, how many children to have, use of FP, and SRH care seeking (Shahabuddin et al., 2016; Shahabuddin et al., 2016; Samandari et al., 2020; Haque et al., 2012; Deb et al., 2011). They end up having teenage pregnancy, shorter birth intervals and higher number of children (Godha et al., 2013; Santhya & Jejeebhoy, 2015; MacQuarrie KLD et al., 2015).

Although social norms are recognised as one of the main drivers of denial of SRHR to married adolescent girls (Coast et al., 2019; Shakya et al., 2019; Wamoyi et al., 2019), social norms theories and approaches to programming are relatively new and there has been little attempt to develop and rigorously test interventions to address such social norms worldwide. In line with other proponents of social norm interventions we argue that in contexts, where norms are significant drivers of decision-making and behaviour, social norm interventions are most likely to be effective in addressing the issues sustainably (Gonzales et al., 2012; Igras et al., 2019). A handful of social norm-based interventions have been developed for addressing adolescent SRHR in LMIC. Most of them are focused on child marriage ([name] et al., 2022), violence (Clark et al., 2017) and female genital mutilation (Cisse et al., 2018). A very few social norm interventions addressing other SRHR issues faced by married adolescent girls have been rigorously evaluated. The two qualitative evaluations deserving mentioning are of CARE projects known as Tesfa (Addis Continental Institute of Public Health, 2018) and Abdiboru (Addis Continental Institute of Public Health, 2016) interventions in Africa. These projects aimed at promoting ASRHR knowledge, positive attitudes and uptake of SRH services empowering the MAGs and working with the communities they live in. One of the most recent social norm interventions addressing ASRHR of married girls was the IMAGINE project of CARE implemented in Bangladesh (CARE, 2019; Grant and Laterra, 2019). Evaluation of all of these CARE projects show some promise. However, none of them were rigorously evaluated.

A lot of programmes have been implemented worldwide and in Bangladesh to empower partnered female adolescents for promoting SRHR. We argue that conceptualization of empowerment in these initiatives were often not grounded in solid theory and evidence. Thus, empowerment programmes for women and girls often fail to include a critical component, namely, movement building and collective agency and critical consciousness, without which empowerment cannot take place in its true sense (Freire, 1973; Yount et al., 2021). Following feminist traditions, we define empowerment as intrinsic power within to overcome dominated consciousness, instrumental power to pursue aspirations, and collective power with others to pursue shared goals (Thomas et al., 2021; Sardenberg, 2008). We are going to address these research and intervention gaps in this project.

At this backdrop, the current study proposes to develop and test Balika Bodhu, a social norm intervention to address the gaps in programming and in the literature combining a comprehensive empowerment programme for MAGs with engagement of other stakeholders to increase demand, access and practice of positive behaviours in relation to SRHR among these MAGs. Balika Bodhu covers married adolescent girls aged 15-19 years.

